#### Sample-specific adaptations

A primary goal of this project is to understand children’s views around the kinds of religious entities, practices, and norms they encounter in their everyday lives [48]. To this end, for each sample we tailor the Child Protocol and Parent Survey to include stimuli that are salient to the particular cultural-religious setting in question, while maintaining a high degree of standardization in the structure and framing of all protocol elements. To make these sample-specific adaptations, each research team conducted semi-structured interviews with local religious experts relevant to their planned samples. As a network, we engaged in an iterative process of selecting stimuli, comparing and discussing choices across research teams, pilot testing, revising network-wide guidelines for stimulus selection, and revising sample-specific stimuli. The details of this process will be discussed in a separate, forthcoming manuscript.

In the current manuscript we present the standard versions and network-guidelines for each element of the study protocol, organized with respect to our three primary research questions. For each protocol element, we also detail the sample-specific adaptations for the five target religions included in US samples, where sample-specific adaptation is complete and data collection is underway.

### Research question 1: How do children represent and reason about religious and supernatural agents?

#### Sorting task: Assessing the familiarity and reality status of religious agents

Building on previous work on children’s understanding of what is real vs. not real [e.g., 49] as well as children’s ability to sort items based on some type of rule [i.e., familiarity and reality status; see, e.g., 50], the Sorting task is designed to assess children’s familiarity with natural, supernatural, and religious agents, and their judgments about which of these agents are real. This task is part of the Child Protocol; see Fig 2.

*Task design and procedure*. To begin the task, the researcher says, “We’re going to talk about a bunch of different things. Your first job is to tell me if you’ve ever heard of the thing I mention. Then, your second job is to tell me if you think the thing is real or not real. Let’s try some.”

Next, the child is presented with two practice trials in a random order. One practice trial involves a familiar agent (“doctors”), and the second practice trial involves the use of a nonsense word that children should indicate is unfamiliar (“breksters”). These practice trials are designed to familiarize children with the task format; to encourage them to use the full range of response options available to them; to encourage them to take the task seriously (i.e., provide sincere responses even if the questions seem silly or unusual); and to establish that the task will include both familiar and unfamiliar and both real and unreal agents.

Immediately following the practice trials, the child is presented with roughly 15–20 test trials in a random order. On each trial, the child is asked two questions about an agent, in a fixed order: “Have you ever heard of [agent]?” (familiarity judgment; response options: “yes” or “no”) and “Is/are [agent] real or not real?” (reality judgment; response options: “real” or “not real”).

The range of agents included in this task is intended to vary across samples to preserve cultural and religious specificity and appropriateness, within certain limits designed to maintain a balanced level of standardization across samples. The aspects that were standardized are described in the following paragraphs; see Table 1 for items selected for each US sample.

**Table 1 pone.0292755.t001:** Sample-specific item selection for the Sorting task, for the five religions included in US samples.

Religion				
*Protestantism*	*Catholicism*	*Church of Jesus Christ of L*.*D*.*S*.	*Judaism*	*Islam*
** *Religious and supernatural agents* **				
God	God	God	God^a^	Allah
Jesus	Jesus	Jesus	Elijah	the Prophet Muhammad
the Holy Spirit	the Holy Spirit	the Holy Spirit	Jesus	Jesus
angels	angels	angels	angels	angels
the Devil	the Devil	the Devil	the Devil	the Devil
ghosts	ghosts	ghosts	ghosts	ghosts
fortune tellers	fortune tellers	fortune tellers	fortune tellers	fortune tellers
** *Fictional agents* **				
fairies	fairies	fairies	fairies	fairies
witches	witches	witches	witches	witches
Santa Claus	Santa Claus	Santa Claus	Santa Claus	Santa Claus
zombies	zombies	zombies	zombies	zombies
** *Natural and scientific agents* **				
germs	germs	germs	germs	germs
robbers	robbers	robbers	robbers	robbers
** *Religious groups* **				
Christian people	Catholic people	members of the Church of Jesus Christ	Jewish people	Muslim people
Muslim people	Muslim people	Muslim people	Christian people	Christian people
** *Attention/comprehension checks* **				
Blambies	Blambies	Blambies	Blambies	Blambies
the Rumber	the Rumber	the Rumber	the Rumber	the Rumber
** *Sample-specific additions* **				
praying to God	praying to God	praying to God	praying to God	praying to God
–	–	prophets	prophets	prophets
–	–	–	–	djinn

Unaffiliated children in the US are shown the version of the protocol that corresponds to the religion with which they are likely most familiar (see main text for details). See main text for descriptions of network-wide guidelines for item selection. “L.D.S.” stands for “Latter-day Saints.”

^a^ If the researcher becomes aware that the child is more familiar with the term “Hashem” or “Adonai” then the more familiar term is used in place of “God” throughout the Child Protocol.

Each version of the protocol contains at least six *religious or supernatural agents* that are widely considered “real” in the cultural-religious setting. These agents include the “Biggest” god [51] in the cultural-religious setting, as well as 1–2 additional prominent religious agents; these agents are also featured later in the protocol in the Property Attributions and Justifications tasks (described in later sections). Beyond this, other religious/supernatural agents include a positive divine being; a negative divine being; dead humans that may or may not be worshiped; and humans with supernatural powers which at least some adults might believe are real.

Each version of the protocol also includes at least three *fictional agents* that are widely considered “fictional” or “fantasy” in the cultural-religious setting. These agents include one human with supernatural powers and two additional agents that are part of local folklore, including at least one agent with fairly “human-like” properties.

To provide a contrast to the religious, supernatural, and fictional agents described above, we include at least two *natural or scientific agents*: scientific entities unobservable by naked eye; and ordinary (non-supernatural) humans engaged in a negatively valenced or antisocial activity.

Each version of the protocol includes at least two *religious groups*, including the child’s own religious group or a locally prevalent religious group, as well as at least one other religious group salient in the local setting. These two religious groups are also featured later in the protocol in the Religious Indicators, Social Essentialism, Norm Violations, and Child as Transmission Agent tasks (described in later sections). For these two trials, the child is asked one additional follow-up question after the familiarity and reality status questions. If the child indicates that they are familiar with the group in question, the follow-up question is, “What do you know about [religious group]?” If the child indicates that they are not familiar with the group in question, the follow-up question is instead, “When I say the word(s) [religious group], what do you think of?”

Finally, each version of the protocol includes two agents intended as *attention/comprehension checks*: a novel category of entities presented in the plural generic (e.g., “Blambies”); and a novel entity presented as a singular individual (e.g., “The Rumber”).

All agents are presented in random order.

Research teams are encouraged to include a mix of specific individuals (e.g., “Santa Claus”) and plural generics (e.g., “zombies”), as relevant in the local language and cultural-religious setting. We do not specify which items should be worded in which way; in other words, we prioritize cultural specificity within a sample over syntactical standardization across samples.

Some research teams also include additional, sample-specific items in this list as desired, in order to capture aspects of the cultural-religious setting beyond what is captured by the standard list of agents. Additional items are randomized along with the other agents in the standard list, with the exception of any additional ethno-religious groups beyond the two described above, which are presented in a random order after the standard list.

In the US samples, this task is estimated to take 5 to 7 minutes with younger participants and 4 to 9 minutes with the oldest participants.

*Adaptation for US samples*. The final set of agents featured in the Sorting task for the five religions included in US samples is presented in Table 1.

*Parallel task for parents/caregivers*. Parents/caregivers complete a modified version of the Sorting task just described. Each parent/caregiver is presented with the same set of agents as their child assessed, in a random order. For each agent, parents/caregivers are asked two questions: “Is/are [agent] real or not real?” (response options: “real,” “not real,” “I have never heard of this”) and “How sure are you that [agent] is/are [real/not real]” (11-point response scale ranging from [0] “I am not sure at all” to [10] “I am extremely sure”).

*Planned analyses*. We hypothesize that children’s familiarity with the agents included in this task will increase with age, and that this increase will be more pronounced for supernatural agents [see 49, 50, 52, 53]. To test this, we will examine the main effect of participant age (4–10 years) on responses to the familiarity question (“Have you heard of [agent]?”), as well as statistical interactions between participant age and agent type (supernatural vs. natural, fictional vs. natural).

We also hypothesize that children will be more likely to indicate that natural agents are real, as compared to fictional and supernatural agents; and that such differences will increase with age [see 49, 50]. To test this, we will examine the main effect of agent type (supernatural vs. natural, fictional vs. natural) on responses to the reality question (“Is/are [agent] real?”), as well as statistical interactions between participant age (4–10 years) and agent type.

Drawing on past literature, we further predict that children’s reality status judgments will be associated with their familiarity judgments [54]. More specifically, we expect that children will be less likely to attribute reality status to agents that are unfamiliar to them.

Additional exploratory analyses will examine relationships among reality judgments, familiarity judgments, and the emotional valence of the agent, and other higher-order statistical interactions. Beyond this, we plan to compare responses across samples from different cultural-religious groups; to compare children’s responses to those of parents/caregivers, to explore relationships between children’s responses and information provided in the Parent Survey; and to explore relationships between this and other tasks included in the Child Protocol (e.g., correlations between reality status judgments and questions about whether a given agent is good or bad).

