#### Property Attributions task: Assessing the role of folk physics, biology, psychology, and sociology in reasoning about religious agents

The Property Attributions task is designed to evaluate conceptualizations of religious and supernatural agents [for similar tasks, see 8,38,55]. This is part of the Child Protocol; see Fig 2.

*Task design and procedure*. The Property Attributions task consists of a 20-item close-ended battery intended to assess participants’ representations of the physical, biological, cognitive-epistemic, social-emotional, and sociological properties and constraints of two to three religious/supernatural agents, as compared to the properties and constraints of ordinary human agents.

The task features the “Biggest” god [51] in the cultural-religious setting as well as 1–2 additional prominent religious agents. These religious/supernatural agents are also featured in the Sorting task (described in the previous section) and in the Justifications task (described in a later section); if a child indicates that they are not familiar with one of these agents in the Sorting Task, this agent is omitted from the Property Attributions and Justifications tasks for that child. Questions about human or human-like prophets and other agents who are not the “Biggest” god are referred to as “Agent 1” for the purposes of this task, and always precede questions about the “Biggest” god (“Agent 2”). Throughout the task, these religious/supernatural agents are compared to an ordinary human (“a person”). See Table 2 for items selected for each US sample.

**Table 2 pone.0292755.t002:** Sample-specific item selection for the Property Attributions and Justifications tasks, for the five religions included in US samples.

	Religion				
Agent	*Protestantism*	*Catholicism*	*Church of Jesus Christ of L*.*D*.*S*.	*Judaism*	*Islam*
*1*	Jesus	Jesus	Jesus	Elijah	the Prophet Muhammad
*2*	God	God	God	God^a^	Allah
*3*	the Holy Spirit	the Holy Spirit	the Holy Spirit	Jesus	Jesus

Unaffiliated children in the US are shown the version of the protocol that corresponds to the religion with which they are likely most familiar (see main text for details). See main text for descriptions of network-wide guidelines for item selection. “L.D.S.” stands for “Latter-day Saints.”

^a^ If the researcher becomes aware that the child is more familiar with the term “Hashem” or “Adonai” then the more familiar term is used in place of “God” throughout the Child Protocol.

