The six properties described above (three religious, three neutral) are used in both blocks of the task. The first block focuses on children’s sense of similarity to the character featured on each trial. The researcher introduces the block by saying, “I’m going to tell you about some kids, and I want to know if they’re like you or different from you. There are no right or wrong answers here—I just want to know what you think.” On each trial, the researcher shows the child the silhouette of the character and reads the corresponding property aloud to the child. The child is then asked two questions in a fixed order: “Is [she/he] like you or different from you?” and “A little bit [like you/different from you] or a lot [like you/different from you]?” These two questions are designed to be combined into a 4-point response scale (“a lot different from me,” “a little bit different from me,” “a little bit like me,” “a lot like me”).

The second block follows an identical design but focuses on the child’s assessment of whether the characters are or are not members of the target religious group. The researcher introduces the block by saying, “Now I’m going to show you those kids again, and this time I want to know something different. I want to know whether they are [target religious group label] or *not* [target religious group label]. It’s ok if you’re not sure—I just want you to make your best guess.” As in the first block, on each trial, the researcher shows the child the silhouette of the character and reads the corresponding property aloud to the child. The child is then asked two questions in a fixed order: “Is [she/he] [target religious group label] or *not* [target religious group label]?” and “Probably [target religious group label/*not* target religious group label] or definitely [target religious group label/*not* target religious group label]?” Again, these two questions are designed to be combined into a 4-point response scale.

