We also expect that children’s responses to religious vs. neutral properties will vary across domains (e.g., that the difference between ascriptions of religious vs. neutral beliefs might function as a more powerful indicator of religious group membership than the difference between behaviors related to religious vs. neutral holidays) [see 64, 65]. To test this hypothesis, we will examine statistical interactions between property type (religious vs. neutral) and indicator type (belief, holiday, prayer-like practice) on children’s responses in the second block of the task.

Developmentally, we hypothesize that children’s tendency to recognize religious indicators and infer religious group membership will increase with age [65–67]. To test this hypothesis, we will examine a statistical interaction between property type (religious vs. neutral) and participant age (4–10 years) on children’s responses in the second block of this task.

We will conduct a parallel set of analyses for data from the first block of this task, in which children are asked to judge how similar the characters are to themselves (“Is [she/he] like you or different from you?”). These analyses will assess whether children judge characters associated with religious vs. neutral properties to be more similar to themselves, and whether this tendency differs across specific religious indicator types (belief, holiday, prayer-like practice) or across the age range of our samples. These analyses will be exploratory; we do not have strong predictions about the strength or direction of these results.

Beyond this, we plan to examine higher-order statistical interactions (e.g., an interaction between property type, indicator type, and participant age); to conduct within-subjects analyses of the relationships between children’s responses in the first and second blocks of this task (i.e., between children’s similarity judgments and their recognition of religious indicators); to compare responses across samples from different cultural-religious groups; to explore relationships between children’s responses in this task and information provided in the Parent Survey; and to examine relationships between this and other tasks included in the Child Protocol.

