** *Non-reference group (Religion Block)* **					
*plural noun form*	Muslims	Muslims	Muslims	Christians	Christians
*adjective form*	Muslim	Muslim	Muslim	Christian	Christian

Unaffiliated children in the US are shown the version of the protocol that corresponds to the religion with which they are likely most familiar (see main text for details). See main text for descriptions of network-wide guidelines for item selection. “L.D.S.” stands for “Latter-day Saints.”

*Parallel tasks with parents/caregivers*. Parents/caregivers complete the religion block of the Social Essentialism task (but no other blocks of this task), and they are asked to indicate their level of certainty for each response on an 11-point scale ranging from [0] “I am not sure at all” to [10] “I am extremely sure.”

*Planned analyses*. Based on previous work [64, 68, 69], we hypothesize that we will observe the highest levels of social essentialism in the gender block and the lowest levels of social essentialism in the wealth block, and that social essentialism in the religion block will be intermediate between these extremes. To test this hypothesis, we will examine the main effect of domain (gender, religion, wealth) on children’s tendency to select “essentialist” responses.

Developmentally, we hypothesize that these differences in social essentialism across domains will increase with age [see, e.g., 68]. To test this hypothesis, we will examine statistical interactions between domain (gender, religion, wealth) and participant age (4–10 years).

In testing these predictions, we plan both to conduct item-level analyses (e.g., examining differences across the four questions included within each domain, or examining domain differences considering each of these four questions separately); and to conduct analyses in which we combine responses across items.

Beyond these predictions, we plan to compare the responses of boy and girl participants, especially in the gender block; to compare responses of children from families varying in socioeconomic status, especially in the wealth block; to compare responses across samples from different cultural-religious groups in all blocks; to compare children’s responses to those of parents/caregivers; to explore relationships between children’s responses in this task and information provided in the Parent Survey; and to examine relationships between this and other tasks included in the Child Protocol.

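### Two planned tests include children who have not heard of the religious group, and the familiarity answer already collected in the Sorting task is not used to show what this does to the result

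*Protocol article*

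**What the plan says.** In the Sorting task (task design and procedure), each child is asked whether they have heard of the child's own or a locally prevalent religious group and of at least one other group. The labels are then reused: "These two religious groups are also featured later in the protocol in the Religious Indicators, Social Essentialism, Norm Violations" and Child as Transmission Agent tasks. A negative answer changes only the wording of the next Sorting question: "If the child indicates that they are not familiar with the group in question, the follow-up question is instead" an open prompt about what the words bring to mind.

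Religious agents are treated differently. In the Property Attributions task, "if a child indicates that they are not familiar with one of these agents in the Sorting Task, this agent is omitted" from that task and from the Justifications task for that child.

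The two tests at issue are these:

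- **Social Essentialism, planned analyses.** The prediction is that gender is highest, wealth lowest and "social essentialism in the religion block will be intermediate between these extremes". The test is the main effect of domain. The answer options are yes, maybe and no, and the article does not say how a 'maybe' is scored.
- **Religious Indicators, planned analyses.** The prediction is that children's "tendency to recognize religious indicators and infer religious group membership will increase with age". The test is the interaction of property type with age in Block 2, where the script to an unsure child is "I just want you to make your best guess".

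Neither test has a familiarity condition. The US exclusion criteria plan no exclusion of data by trial or task. The familiarity check that closes Norm Violations concerns the two norms, not the group label.

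**The concern.** A child who does not know a label such as Muslim, Catholic or member of the Church of Jesus Christ has little basis for saying whether a character is one, or whether such people are born that way. The comparison labels in Social Essentialism (girls and boys, rich and poor people) are everyday words. Label ignorance therefore falls on one of the three domains, and probably on the youngest children. The Sorting section itself predicts that familiarity with its agents rises with age. It does not name the religious groups in that prediction, but they are items of the same task.

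Two readings could be affected. The religion block could move relative to gender and wealth for reasons of vocabulary. And the Religious Indicators age interaction could reflect learning of the label, recognition of the beliefs, holidays and practices, or both, with nothing in the stated test to tell them apart. The variable that would show the difference is already recorded for every child.

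**Working it through.** **Inputs from the article.** US samples of 75 to 100 per group; six groups give 6 × 75 = 450 to 6 × 100 = 600, which reproduces the stated total. Social Essentialism has four questions per block; Religious Indicators has three religious and three neutral items.

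**Inputs assumed.** The article gives no familiarity rates, effect sizes or alpha. Let u be the share who do not know the label, falling linearly with age; p the rate among children who know it; g the rate among those who do not. Essentialist rates: gender 0.80, wealth 0.20. Rates of answering 'member' among children who know the label: 0.85 for religious and 0.35 for neutral items at every age; 0.5 for guessers. Ages uniform from 4 to 11; two-sided 0.05; 1,000 to 2,000 runs per setting.

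**Social Essentialism, expected shift.** Observed rate = (1 − u)p + ug, so the shift is u(g − p). With u = 0.4:

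- Religion equal to gender (p = 0.80): 0.48 + 0.4/3 = 0.61 at g = 1/3; 0.48 + 0.20 = 0.68 at g = 1/2; 0.48 at g = 0. All lie between 0.20 and 0.80.
- Religion equal to wealth (p = 0.20): 0.12 + 0.4/3 = 0.25 at g = 1/3; 0.12 + 0.20 = 0.32 at g = 1/2; 0.12 at g = 0, which is below wealth.

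The pull is small when g is near p. A child who says yes to everything scores about 3/4, because one of the four questions is reverse-worded; at p = 0.80 the shift is then 0.4 × (0.75 − 0.80) = −0.02.

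**Chance that both steps of gender > religion > wealth are significant although religion equals one of the extremes** (paired t-tests):

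| Religion truly equals | u, age 4 to age 10 | g | n = 75 | n = 100 | n = 450 |
|---|---|---|---|---|---|
| gender | 30% to 0% | 1/3 | 37% | 44% | 98% |
| gender | 30% to 0% | 1/2 | 18% | 22% | 78% |
| gender | 60% to 10% | 1/3 | 93% | 97% | 100% |
| gender | 60% to 10% | 1/2 | 68% | 80% | 100% |
| wealth | 30% to 0% | 1/3 | 7% | 10% | 26% |
| wealth | 30% to 0% | 1/2 | 19% | 22% | 76% |
| wealth | 60% to 10% | 1/3 | 21% | 31% | 83% |
| wealth | 60% to 10% | 1/2 | 64% | 82% | 100% |

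With u = 0 the figure is 2% to 3%.

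**Sensitivity of the wealth case.** With religion and wealth both at 0.30, and u falling from 40% to 5% or from 60% to 10%, g = 1/3 gives a false order in only about 3% to 5% of samples. If non-knowers say 'maybe' and it counts as non-essentialist (g = 0), religion falls significantly below wealth in 45% to 84% of samples of 75, against the prediction.

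**Religious Indicators.** Guessers show no religious-minus-neutral gap, so the observed gap is (1 − u)(0.85 − 0.35). Chance of a significant positive age interaction with no age change among children who know the label:

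| u, age 4 to age 10 | Gap, age 4 to age 10 | n = 75 | n = 100 | n = 450 |
|---|---|---|---|---|
| 30% to 0% | 0.35 to 0.50 | 19% | 23% | 74% |
| 50% to 5% | 0.25 to 0.47 | 35% | 43% | 97% |
| 70% to 10% | 0.15 to 0.45 | 50% | 67% | over 99% |

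Among only the children who know the label it is 1.9% to 3.0%, close to the nominal 2.5% in one direction. The simulation uses a yes/no answer, whereas the task builds a four-point scale.

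**The case against.** The strongest objection concerns Religious Indicators. The task is meant to assess knowledge of religious indicators, and the hypothesis covers both recognising them and inferring membership. A child who has not learned the word Catholic cannot infer that someone is Catholic, so learning the label is one way the hypothesis becomes true. This stands: a reader might infer that an age interaction produced by label learning is a false confirmation, and the article does not support that. What remains is that the stated test cannot say which part of recognition has grown.

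On Social Essentialism, the script tells the child that each group's members share a religion before the questions begin, and the groups are chosen to be the child's own, locally prevalent or locally salient. Non-knowers need not guess at random, and large unfamiliarity is not established. This also stands, and it limits the size. It carries less weight for unaffiliated children, because one who knows no religion is given the Protestant version.

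The article describes the study as largely exploratory, names effects rather than full models, and plans to relate tasks to one another. That clause would allow the Sorting answer to be used, but it sits outside the stated hypothesis tests and does not mention label familiarity. A reader might also take the agent rule and the group rule for a contradiction. They govern different tasks, so the difference is one of treatment, not an inconsistency of fact.

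**Conclusion.** The point holds as a cheap improvement. The plan collects label familiarity, drops unfamiliar agents from later tasks, keeps children unfamiliar with a group in two stated tests, and does not say that the results will be shown by familiarity.

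The size rests on assumed unfamiliarity that falls with age. If children who know the labels rate religion like gender, the religion block is pulled down to an apparently intermediate place, provided non-knowers' essentialist rate is clearly below that for gender. If they rate religion like wealth, the direction depends on how 'maybe' is scored, so it cannot be said that ignorance of the label generally produces the predicted order. At 75 to 100 children with modest unfamiliarity the artefact often does not reach significance; in the pooled US sample it is more likely to. It would not explain a widening of all the domain differences with age, because falling unfamiliarity shrinks a false gap between religion and the domain it truly matches.

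Two further inferences go too far. The calculations do not show that either prediction would be confirmed by vocabulary alone in the actual data. Nor do they cover the scope question in Norm Violations, for which no effect has been shown.

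**What to change.** For the religion block of Social Essentialism and Block 2 of Religious Indicators, add the child's Sorting familiarity answer as a moderator: both named groups for Social Essentialism, the target group for Religious Indicators. Report the domain-order estimates and the property-type-by-age estimate, with intervals, among children who have heard of the label(s), beside the all-children result. Use the existing Sorting follow-up about what the child knows of the group to check the yes answers.

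Interpret by comparing the two estimates, not by whether the smaller subset reaches significance. A non-significant result among children who know the label should not be relabelled as label learning: with real growth among those children, the restricted analysis detected it in only about 36% to 49% of simulated samples of 75, depending on the set-up.

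The cost is analysis wording; no new data are needed. The restricted estimate has fewer young children and wider intervals. If unfamiliarity falls from 40% to 5%, the mean is (40 + 5)/2 = 22.5%, so about 78% of children are kept; from 60% to 10% it is (60 + 10)/2 = 35%, so about 65% are kept. The all-children analysis stays in place.
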